## Abstract

**Background:**

Thumb carpometacarpal osteoarthritis (CMC OA) is characterized by chronic progressive degeneration of the joint cartilage, with high prevalence. Patients present with pain at the base of the thumb, morning stiffness, and muscle weakness, symptoms that affect hand function and therefore interfere in activities and social participation. Movements that involve grip or lateral pinch are the most affected and directly impact independence, self-care, and leisure activities. In the literature consulted, several protocols with exercises for these patients were found. However, most do not compare the same intervention modality and only provide basic methodological information, with no consistent information on training load and load progression. In addition, most protocols only address the strengthening of the abductor and extensor thumb muscles and pinching or grasping exercises. However, some biomechanical and electromyographic studies have demonstrated the important role of the first dorsal interosseous muscles as stabilizers of the thumb carpometacarpal joint.

**Methods:**

This is a randomized, controlled, double-blind, and parallel clinical trial that will include 56 participants, over 40 years old, with radiographic evidence of thumb base osteoarthritis. Participants will be randomly allocated into two groups: control and intervention. The following evaluations will be conducted: the Australian/Canadian Hand Osteoarthritis Index, Canadian Occupational Performance Measure, Nine-Hole Peg Test, grip and pinch strength associated with muscle activation assessment, and Bilateral Upper Limb Function Test at four different times: baseline, session 13, session 18, and follow-up. Treatment will take place over 6 weeks, with reassessments in the fourth and sixth weeks and 3 months after the end of the intervention (follow-up). Qualitative variables will be expressed as frequency and percentage, and quantitative variables as mean and standard deviation. Intergroup comparison of the intervention will be performed by repeated measures ANOVA, considering the effect of the two groups and four assessments, and interactions between them.

**Discussion:**

This study will demonstrate whether the specific strengthening of the first dorsal interosseous muscle has a superior and positive effect on the clinical picture of patients with CMC OA. Additionally, if specific strengthening of the muscle is not superior to the traditional protocol in the literature, it will also be determined whether the two protocols are equivalent in terms of the best clinical picture.

**Trial registration:**

Brazilian Registry of Clinical Trials (ReBEC) RBR-8kgqk4. Prospectively registered on 15 January 2020

## Introduction

### Background and rationale {6a}

Thumb carpometacarpal (CMC) osteoarthritis (OA) is a health condition characterized by progressive degeneration of the articular cartilage, subchondral bone sclerosis, ligament laxity, and osteophyte formation at the base of the first metacarpal [1]. It is a chronic and highly prevalent disease, especially in postmenopausal women. The Framingham Study found that 2% of men and 7% of women aged 40 to 84 years had symptomatic CMC OA, while radiographic CMC OA was present in 30% of men and 33% of women in the same study [2]. Another investigation estimated the prevalence of CMC OA to be 13% in people aged 41–50 years, increasing to 68% in 71- to 80-year-olds [3].

Patients with CMC OA have a lower pain threshold, pain at the base of the thumb or thenar eminence, morning stiffness, and muscle weakness, especially in the abductor pollicis and extensor muscles of the index finger [4]. These symptoms affect hand function, thereby interfering in the activities and social participation of patients [5]. The disease causes significant social and personal restrictions, reduced quality of life [6], and incapacity for work [7]. When compared to OA in the other fingers, patients with CMC OA receive more anti-inflammatory drugs and have a worse prognosis because they experience more severe pain and greater physical dysfunction [7]. Movements involving grip or lateral pinch are the most affected and directly impact independence, self-care, and leisure activities [8]. Activities reported as the most difficult to perform are opening jars, writing, turning keys in locks, opening food packages, wringing clothes, and carrying heavy objects between the thumb and fingers [9, 10].

The European League Against Rheumatism (EULAR) (2018) recommends that surgery for patients with CMC OA only be considered in the event of important structural abnormalities and when conservative treatment has not been effective in reducing pain and improving dysfunction [11–13]. In the early stages of the disease, conservative treatment has a beneficial effect on symptom relief [12] and includes patient education techniques, use of auxiliary devices, orthoses, and exercises [11]. However, the latest systematic review and meta-analysis on physical therapies (orthosis, mobilizations, neurodynamic techniques, and physical exercises) for patients with CMC OA highlighted that, despite the evidence on the unimodal or multimodal use of these treatments, only 5 studies were identified, suggesting that new high-quality randomized clinical trials are needed [14].

Although there are several exercise protocols for patients with CMC OA in the literature, most do not compare the same intervention modality [4, 15–18]. Additionally, the protocols only present basic methodological information, such as how many times a week the exercises should be performed and the number of repetitions for each exercise. However, there is no consistent information about training load and load progression methods. The majority of the protocols used the number of repetitions based on the weeks of treatment as an exercise progression method, that is, progression is general and not tailored to the patient’s capacity [4, 16, 17]. This contrasts with EULAR recommendations, which stipulate that OA management should be individualized [11].

The exercises proposed in the protocols describe the active movement of the CMC, proximal (PIP) and distal interphalangeal (DIP) joints of the thumb and other fingers, strengthening of the thumb abductor and extensor muscles, and pinching or gripping exercises [15, 17–19]. However, ligament laxity and joint hypermobility are known to be important etiological factors for the development of the disease [20, 21]. This laxity favors joint subluxation, which results in incongruity and abnormal joint loading, which may contribute to the development of CMC OA [22, 23]. In this respect, biomechanics and electromyography studies have demonstrated the important role of the opposing thumb and first dorsal interosseous muscle (1st DI) as stabilizers of this joint [24, 25].

The action of the 1st DI is described as antagonistic to the subluxation forces of the adductor pollicis muscle, that is, it centers the base of the 1st metacarpal on the trapezius [24–26]. As such, including the 1st DI muscle in CMC OA protocols seems to have important clinical significance. However, few protocols currently include exercises for this muscle [15, 27, 28], and there are no studies comparing two equal modalities in order to assess the effect of strengthening this muscle or not.

Thus, it is essential to carry out a study that adds to the physical exercise protocol the strengthening of the 1st DI muscles, in order to verify the effect of this strengthening on the clinical condition of patients with OA CMC. Therefore, it seems relevant, scientifically and clinically, to compare two protocols that use the same treatment technique (physical exercises) with the addition of the strengthening of the 1st DI. Furthermore, it is extremely important that the protocols clearly present the load used and the load progression parameters, as these variables can influence the result of the treatment.

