### Objectives {7}

The main objective of this randomized clinical trial will be to verify whether a protocol with load increment, focusing on strengthening the 1st dorsal interosseous, will be effective for pain relief and improvement of strength and function for patients with OA CMC.

The secondary objectives will be to compare the clinical characteristics of the patients evaluated in the study, between the two treatment groups: such as pain at rest, pain during pinch movement and during activities, activity and social participation, manual dexterity, hand function, hand strength, grip and pinch, and muscle activation.

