### Interventions

#### Explanation for the choice of comparators {6b}

The intervention group will perform manual thumb joint mobility and 1st DI strengthening exercises. The control group will be submitted to a standard manual exercise protocol with proven benefits, previously published in the literature. All the sessions for both groups will be carried out in person, on non-consecutive days, with one of the two physiotherapists trained to apply the protocols.

The intervention will take place over a 6-week period, with three 45-min sessions a week, totaling 18 treatment sessions. The first session will take place 1 week after the baseline assessment. Both intervention protocols will be applied based on the shaping method for exercise load progression, as described below.

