#### Intervention description {11a}

##### Control group

The control group will perform a manual exercise protocol with traditional exercises for CMC OA patients, based on the protocol of Gravas et al [18]. The hand mobility and stretching exercises will be executed in the order described in the protocol, with 10 repetitions each, throughout the treatment period.

The strength and joint stability exercise will also be performed as described, but the volume and load progression will be different. Progression parameters will also be used for the load. As such, for exercises 4, 5, and 6:
Volume: 10 repetitions of 15 s eachFeedback measurement parameter (FMP): number of repetitions performed in 15 sProgression parameter 1 (PP1): increase the resistance of the elastic (different color elastic) or the mass

It is important to emphasize that exercise 5 will be performed with a silicone grip ball in order to ensure optimal load progression.

The exercises will be applied in the order described in the original protocol.

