## Discussion

This study will demonstrate whether specific strengthening of the first dorsal interosseous muscle has a superior and positive effect on the clinical picture of patients with CMC OA. Additionally, if specific strengthening of this muscle is not superior to the traditional protocol in the literature, it will also be determined whether the two protocols are equivalent in terms of the best clinical picture. This will be analyzed based on possible changes in some symptoms (i.e., pain, function, activity, and participation) during the treatment period (4 weeks and 6 weeks), or 3 months after its completion.

To date, there are no guidelines for the treatment of CMC OA. The most recent update of treatment recommendations comes from the EULAR, which published an update on management recommendations for patients with hand osteoarthritis in 2018 [11]. However, the only recommendation for patients with OA at the base of the thumb is the use of orthosis for symptom relief. In general, the article indicates that the main goal of hand osteoarthritis treatment is to control symptoms such as pain and stiffness and optimize hand function in order to maximize activity, participation, and quality of life. Following this principle and developing a protocol involving muscle strengthening through functional activities in specific cases of CMC OA seems to be important. In addition, our protocol involves strengthening a muscle considered fundamental in stabilizing the joint involved, a significant differential.

Finally, it is worth mentioning that systematic reviews on the subject emphasize the low quality of clinical trials, which can interfere with the reliability and clinical applicability of manual exercises. As such, our protocol could contribute to the development of a reliable methodological procedure to guide physiotherapists in clinical practice, providing clear information on how to perform the exercises, training volume, and load progression.

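### The arms are two different exercise programmes, so the trial can compare the packages but cannot isolate the effect of first dorsal interosseous (1st DI) strengthening

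*Protocol article*

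**What the plan says.** Background and rationale {6a} says the study "adds to the physical exercise protocol the strengthening of the 1st DI muscles, in order to verify the effect of this strengthening". It then describes a comparison of two protocols that share one technique, physical exercise, "with the addition of the strengthening of the 1st DI", and names as the gap in the literature the lack of like-for-like comparisons with and without work on this muscle. The Discussion promises: "This study will demonstrate whether specific strengthening of the first dorsal interosseous muscle has a superior and positive effect". The Discussion part of the Abstract makes nearly the same statement.

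The main objective in Objectives {7} is worded differently. It is to "verify whether a protocol with load increment, focusing on strengthening the 1st dorsal interosseous, will be effective for pain relief", which concerns a whole protocol.

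On the arms, Explanation for the choice of comparators {6b} says: "The intervention group will perform manual thumb joint mobility and 1st DI strengthening exercises". The control arm receives a separate published programme. Under Control group: "The hand mobility and stretching exercises will be executed in the order described in the protocol". Strength and stability exercises 4, 5 and 6 are added, for which "the volume and load progression will be different" from the source protocol.

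**The concern.** The rationale describes a comparison of an exercise programme with that same programme plus 1st DI strengthening. In such a design the between-arm difference estimates the effect of the added component. The arms as described are instead a substitution: one programme replaces another. If the Discussion statement is carried into the results paper, a difference produced by two packages would be reported as the effect of strengthening one muscle. The error can run in either direction. A positive result might come from the other changes. A null result might hide a 1st DI benefit that was offset by losing the control exercises.

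**Working it through.** The plan gives no figure on this point, so the check sets the descriptions of the arms side by side.

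| Feature | Control group | Intervention group |
|---|---|---|
| Stretching | Yes, 10 repetitions of each exercise | None listed |
| Control strength/stability exercises 4–6, exercise 5 with a grip ball | Yes | None listed |
| 1st DI-focused tasks | Not described | Elastic, Styrofoam ball, stars, drawers, aquarium net |
| Volume of strengthening | 10 × 15 s for each of three exercises | 10 × 15 s, 10 × 30 s, or 10 repetitions, depending on the task |
| Progression parameters | One (PP1) | Two (PP1 and PP2) for four of the five listed tasks, one for the fifth |
| Session pattern | Same order throughout | Alternating even and odd sessions |
| Shared by both | 18 sessions of 45 min, the same two physiotherapists, shaping method for progression | As control |

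**Volume, where it is timed.** If each of control exercises 4 to 6 is done once per session, timed strengthening is 3 × 10 × 15 s = 450 s per session. In the intervention arm the one timed task gives 10 × 15 s = 150 s in an even session and 10 × 30 s = 300 s in an odd session. The repetition-counted tasks come on top and have no fixed duration. These figures show that the volumes are specified differently. They do not show which arm does more in total.

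**What the contrast estimates.** Let D be the effect of the 1st DI work, S that of stretching, G that of control exercises 4 to 6, and V that of the differences in volume and progression. Take the simplest case, in which effects add up without interaction.

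- Add-on design, as the rationale frames it: Δ = D.
- Arms as described: Δ = D − S − G + V.

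The trial yields one estimate of Δ per outcome and time point. That is one equation with four unknowns.

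- If Δ = 0, then D = S + G − V, which may be above zero.
- If Δ > 0, D may still be zero, provided V > S + G.

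A larger sample narrows the interval around Δ but does not separate its parts. V cannot be set to zero on the document's own reasoning, because Background and rationale {6a} says load and progression can affect the result.

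**The case against.** The strongest reply is that the operative question is already about programmes. The main objective concerns a protocol focused on the 1st DI, and the secondary objectives compare the two treatment groups. The sentence after the Discussion promise sets specific strengthening against the traditional protocol and speaks of two protocols, so it can be read as shorthand for the package. Comparing a whole programme with an active comparator matched for session number and length is also a legitimate design. All of this stands. It shows that the design is sound, but it does not account for the rationale's wording of adding the strengthening in order to verify its effect. That wording and the Discussion sentence still attribute the result to the muscle.

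A reader might infer more than the documents support:

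- *The trial cannot answer its question.* Not so: the programme-level objective is answerable with these arms.
- *The mobility exercises differ as well.* This cannot be verified. The control list is in a cited source that is not shown, and some exercises may overlap. Whether control exercises 4 to 6 also load the 1st DI is unknown for the same reason.
- *Modifying the published control programme is a fault.* The modification is disclosed, and giving both arms load progression makes them more alike.
- *1st DI activation should become merely supportive.* Primary outcomes {12} lists it as primary, and nothing here justifies changing that.

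The intervention text announces six strengthening exercises, while the text at hand lists five. Statements about what that arm lacks therefore apply to the listed exercises. The summary under {6b} still describes the arm as mobility and 1st DI work only.

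**Conclusion.** The point holds as one of attribution. The rationale and the two discussion statements ascribe to the design a property it does not have, namely isolation of the 1st DI effect. At least two named components (stretching, and control exercises 4 to 6) change between arms together with the 1st DI work, as do volume and progression parameters. The share due to the 1st DI is not identifiable from two arms at any sample size. The randomised comparison of the two programmes as packages remains valid, and so does the main objective.

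This rests on reading the intervention arm as described, that is, without the control programme running alongside. Nothing in the protocol article says otherwise.

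**What to change.** Keep the arms. Reconcile Background and rationale {6a} with the Interventions section by restating the rationale, the Discussion of the Abstract and the main Discussion along these lines:

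> The trial compares a 1st DI-focused exercise programme with a modified traditional exercise programme, both with load progression. A difference between the groups, or the absence of one, applies to the programmes as delivered and cannot be assigned to the 1st DI component alone.

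The wording of Objectives {7} and the primary status of the 1st DI activation outcome need no change on this account. Arms, randomisation, sample size and analysis are untouched. The cost is a narrower claim: the results paper may speak about a programme focused on this muscle, but not about the isolated effect of strengthening it.

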### Objectives {7}

The main objective of this randomized clinical trial will be to verify whether a protocol with load increment, focusing on strengthening the 1st dorsal interosseous, will be effective for pain relief and improvement of strength and function for patients with OA CMC.

The secondary objectives will be to compare the clinical characteristics of the patients evaluated in the study, between the two treatment groups: such as pain at rest, pain during pinch movement and during activities, activity and social participation, manual dexterity, hand function, hand strength, grip and pinch, and muscle activation.

### Trial design {8}

This is a randomized, controlled, double-blind (evaluator and patient), and parallel clinical trial. There will be 6 weeks of treatment, with reassessments in the fourth and sixth weeks and 3 months after the end of the intervention (follow-up), as shown in the study design flowchart (Fig. 1). The planning of this project followed the guidelines of the Consolidated Standards of Reporting Trials (CONSORT) and Standard Protocol Items: Recommendations for Interventional Trials (SPIRIT) guidelines.

**Fig. 1 Fig1:**
[figure not shown]
Study design flowchart

## Methods: participants, interventions, and outcomes

### Study setting {9}

The trial is underway in the Research Laboratory in Rheumatology and Hand Rehabilitation, in the Physiotherapy Department of the Federal University of São Carlos (UFSCar) in São Carlos, Brazil.

Participants from the community of São Carlos, Brazil, will be invited to participate in the study. Participants will be recruited from social media, local and regional orthopedic and rheumatology clinics, newspaper and magazine advertisements, and leaflets posted on bulletin boards. After declaring an interest, participants will be phone interviewed by the principal investigator to see if they meet any non-inclusion criteria. If they are considered eligible, a face-to-face evaluation will be scheduled to confirm the inclusion criteria for the study.

### Eligibility criteria {10}

#### Inclusion criteria

Participants will be eligible for the study if they meet all the following inclusion criteria [17]: age over 40 years, radiographic evidence of thumb base OA read by a trained rheumatologist (Eaton-Littler-Burton criteria), normal score in the Mini-Mental State Examination (MMSE) according to schooling level [29], and average pain ≥ 30 on a 100-mm visual analog scale (VAS), where 0 is no pain and 100 the worst pain imaginable, over the past 30 days and in the 48 h prior to baseline assessment. In cases of bilateral OA TMC, the most severely affected hand will be included (according to VAS scores). If the pain scores are the same for both hands, participants will be asked to designate the worst hand (i.e., that causes the most problems, either dominant or non-dominant).

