#### Non-inclusion criteria

Participants who meet any of the following criteria will not be included: known diagnosis of crystal arthritis, autoimmune arthritis, hemochromatosis, or fibromyalgia; hand surgery in the past 6 months or scheduled in the next 6 months; intra-articular hyaluronic acid injection in the affected joint in the past 6 months; intra-articular steroid injection in the affected joint in the past month; significant injury to the affected joint in the past 6 months; any other self-reported hand condition that likely contributes to pain at the base of the thumb; poor general health likely to interfere with compliance or assessments, judged by the investigator; women who are pregnant or breastfeeding; or current use of any of the study interventions.

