### Intervention assignment: allocation

#### Sequence generation {16a}

Individuals who agree to take part in the study and meet all the study criteria will be assigned to the intervention or control group by 1:1 allocation, according to computer-generated randomization, using block sizes of 4 and 6. The two physiotherapists who will apply the interventions will also be randomized in order to avoid bias in blinding.

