#### Implementation {16c}

All patients who give consent for participation and who fulfill the inclusion criteria will be assigned to the intervention group or control group through a 1: 1 allocation, according to computer-generated randomization, using blocks of sizes 4 and 6. A Master’s student not involved in participant assessment will prepare the sequence generation and envelopes. The study coordinator will open the envelopes only after the enrolled participant completes all baseline assessments. The estimated time between baseline assessments and allocation will not exceed 5 days. The envelopes will identify the physiotherapist to perform the intervention and which intervention the participant has been assigned to.

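### Radiographic stage is read at entry and linked by the rationale to benefit, yet it is neither a randomisation stratum nor a model term

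*Protocol article*

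**What the plan says.** - **Entry (Inclusion criteria).** The radiographic criterion is "radiographic evidence of thumb base OA read by a trained rheumatologist (Eaton-Littler-Burton criteria". A staging system is named and no stage range is set. The nearest structural restriction, under Non-inclusion criteria, is "hand surgery in the past 6 months or scheduled in the next 6 months".
- **Rationale (Background and rationale {6a}).** The article states: "In the early stages of the disease, conservative treatment has a beneficial effect on symptom relief". On mechanism it says: "The action of the 1st DI is described as antagonistic to the subluxation forces of the adductor pollicis muscle", and adds that "it centers the base of the 1st metacarpal on the trapezius".
- **Allocation.** Sequence generation {16a} gives 1:1 allocation "according to computer-generated randomization, using block sizes of 4 and 6". Implementation {16c} repeats this: "according to computer-generated randomization, using blocks of sizes 4 and 6". Neither section names a stratification factor.
- **Analysis.** Statistical methods {20a} specifies a mixed-model ANOVA for repeated measures with group, time and their interaction. Section {20b} rules out additional analyses.
- **Size.** Sample size {14} plans 56 participants, 28 per arm, of whom 46 are needed for analysis.

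**The concern.** The article gives its own reason to treat stage as a possible predictor of response: it describes conservative treatment as helpful early in the disease, and the muscle under test as acting against subluxation. A rheumatologist applies a staging system to each radiograph before randomisation, so the information should be to hand at almost no cost. It is then used in neither allocation nor analysis.

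With 28 per arm, the share of advanced joints can differ noticeably between arms. If response varies with stage, such a gap would move the observed difference in pain, function or pinch strength. A reader of the results could not easily separate that movement from an effect of strengthening the first dorsal interosseous. Any variation in change that stage explains would also stay in the error term.

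**Working it through.** **Inputs**
- From the article: N = 56, 28 per arm, blocks of 4 and 6, 1:1, no stratum.
- Assumed: the advanced-stage share, which the article does not give. The shares used are 30%, 40% and 50% (17, 22 and 28 of 56), with 20% (11 of 56) as a sensitivity value.
- Assumed: each block is of size 4 or 6 with equal chance.

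The article states no figure for stage balance, so there is none to reproduce.

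**Step 1: fixed 28 v 28 split.** Let X be the number of advanced-stage patients in one arm and K the total. X is hypergeometric with P(X = x) = C(K, x)·C(56 − K, 28 − x) / C(56, 28), and the gap in patients is |2X − K|.
- K = 28: P(gap ≥ 6 patients, 6/28 = 21 points) = 0.181; P(gap ≥ 8, 29 points) = 0.060.
- K = 17: P(gap ≥ 5 patients, 5/28 = 18 points) = 0.245. The gap must be odd, so the next value is 7 patients (25 points), with probability 0.080.

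**Step 2: the planned blocks.** Blocks of 4 and 6 can leave the last block unfinished at patient 56. The split is then 28:28 with probability 0.77 and 27:29 or 29:27 with probability 0.11 each. Averaging the hypergeometric probability over these splits gives:

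| Assumed advanced share | P(gap ≥ 20 points), fixed 28:28 | P(gap ≥ 20 points), blocks of 4/6 |
|---|---|---|
| 20% (11) | 0.040 | 0.041 |
| 30% (17) | 0.080 | 0.095 |
| 40% (22) | 0.171 | 0.155 |
| 50% (28) | 0.181 | 0.164 |

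A simulation of 40,000 allocations per share with the same blocks agrees (0.040, 0.096, 0.154 and 0.161).

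**Step 3: the same blocks within two strata.** An unfinished block of 6 can leave at most 3 patients' difference in a stratum. The worst case is 3 one way in one stratum and 3 the other way in the other. With K = 17 that is 10 v 7 advanced in arms of 28, a gap of 3/28 = 10.7 points. This has probability about 0.0002. With K = 22 or 28 the parity limits the gap to 2/28 = 7.1 points. A gap of 20 points cannot occur.

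**Step 4: what a gap does to the estimate.** Let D be the difference in mean change between advanced and early disease. A gap g shifts the observed treatment difference by g × D. With g = 6/28 the shift is 0.21 × D. The article gives no value for D, so the shift cannot be put in mm or kg.

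**Step 5: which model term matters.** Write outcome = group + time + group-by-time + stage + error. With complete data, the group-by-time test uses within-patient contrasts. A stage main effect is constant within a patient and cancels from them, so adding it alone leaves that test unchanged. Only stage-by-time, or equivalently stage as a covariate for the change score, acts on the primary change outcomes.

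**The case against.** Unstratified permuted blocks in a single-site trial of 56 are legitimate, and broad eligibility is a defensible choice. Chance imbalance is not bias, and the unadjusted test keeps its type I error. The primary outcomes are changes from baseline, so stable stage-related differences in level cancel; only a stage-dependent change would matter, and the article offers no estimate of one. All of this stands, and it limits the point to precision and interpretation.

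A reader might go further and infer that the protocol contradicts itself by admitting advanced joints. The text does not support that. The background says conservative treatment helps early on, not that it fails later. Its surgery statement requires both structural abnormality and failed conservative treatment. The centring mechanism is described without any claim that it stops working in advanced joints. Excluding patients with scheduled surgery may also remove some with severe disease. So stage is a factor the article links to benefit, not one it says determines response.

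Nor does it follow that stage goes unrecorded. The baseline form is described with illustrative lists, so the stage may well be written down.

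It may also be said that covariates belong in an analysis plan that is not shown. That has weight for the model term. It has less for allocation, because the article describes the randomisation down to block sizes and envelope contents, twice, without a stratum.

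**Conclusion.** The point holds as a modest design improvement. The article links stage to benefit and applies a staging system at entry, but uses stage in neither allocation nor model. For an advanced share of 30% to 50%, the planned blocks give a gap of 20 points or more in about 10% to 16% of allocations; at 20% the figure is about 4%. Stratifying caps the gap at about 11 points. These figures rest on the assumed share, a two-level stage and equal use of the two block sizes. They measure the chance of imbalance, not the size of any distortion, which depends on an unknown difference in change between stages. Neither the validity of the test nor the choice of eligible population is in question.

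**What to change.** Keep the eligible population and N = 56.

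1. Record the Eaton-Littler-Burton stage of the study thumb at entry.
2. Run the existing blocks of 4 and 6 within two stage strata, lower and higher, with the cut fixed before recruitment.
3. Adjust the primary change-from-baseline comparisons for the stratum. In the repeated-measures model include both stage and stage-by-time, because stage alone does not alter the group-by-time test.

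Study setting {9} describes the trial as underway, while Trial status reports recruitment postponed. If allocation has begun, leave the randomisation as it is and make only the stage adjustment, specified before unblinding.

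**Cost.** A second set of envelopes; the stage must be known before the envelope is opened; and with two strata and four assessments, one degree of freedom for stage and three for stage-by-time. Implementation {16c} opens envelopes only after all baseline assessments, so the reading should be available in time.
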